### 2.6. Clinical and Psychosocial Assessments

Clinical, anthropometric, and psychosocial assessments will be completed during the baseline study visit, prior to initiation of home sleep monitoring. Height and weight will be obtained using standard clinical procedures and used to calculate body mass index (BMI, kg/m^2^). Airway assessments will include the Mallampati classification and Brodsky tonsillar grading scale, both of which have been associated with upper airway obstruction and SDB risk in pediatric populations. Two calibrated examiners will independently perform Mallampati and Brodsky assessments blinded to each other’s scores and to the PSQ results. Discrepancies will be resolved by consensus review. All clinical assessments will be performed by trained study personnel using standardized procedures.

Psychosocial functioning will be assessed using validated self-report instruments administered electronically. Symptoms of anxiety and depression will be measured using the Revised Children’s Anxiety and Depression Scale-Short Version (RCADS-25), a 25-item self-report measure scored on a 4-point Likert scale (0 = never to 3 = always), yielding separate anxiety and depression subscale scores with higher values indicating greater symptom severity [37,38]. Perceived stress will be assessed using the Perceived Stress Scale for Children (PSS-C), a 13-item self-report measure scored on a 4-point Likert scale, with higher total scores reflecting greater perceived stress [39]. Daytime sleepiness will be evaluated using the Sleepiness Scale of the Children’s Report of Sleep Patterns (CRSP-S), a validated self-report measure of daytime sleepiness for school-aged children with demonstrated reliability and construct validity [40].

Detailed administration procedures, scoring algorithms, handling of missing data, interpretation thresholds, and psychometric properties for each psychosocial instrument (RCADS-25, PSS-C, CRSP-S) are provided as Supplementary Materials.

### 2.7. Exploratory Craniofacial Assessment

Exploratory craniofacial analyses will be conducted among participants with clinically available lateral cephalometric radiographs obtained as part of routine dental or orthodontic care. No radiographs will be obtained specifically for research purposes, and study participation will not require the availability of a cephalometric radiograph. Clinically obtained lateral cephalometric radiograph within six months prior to or within six months after the baseline study visit or enrollment will be used when available in the electronic medical record. For participants with multiple available radiographs, the image obtained closest to the baseline study visit will be selected for analysis.

Cephalometric measurements will be obtained using standardized landmark identification and tracing procedures by calibrated study personnel. Variables of interest will include dental and skeletal planar values and skeletal vertical and anterior–posterior values relevant to upper airway patency. Because cephalometric imaging will only be available for a subset of participants and was not obtained under a standardized research imaging protocol, these analyses are considered exploratory and hypothesis-generating.

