### 2.3. Screening and Eligibility

Children meeting all inclusion criteria and none of the exclusion criteria will be eligible for enrollment. The age range of 8–13 years was selected to capture a developmental period when SDB may influence craniofacial growth and psychosocial functioning while also allowing reliable completion of self-report measures.

Eligible participants will be children aged 8–13 years receiving care at the UNC ASOD Pediatric Dentistry Clinic with an American Society of Anesthesiologists (ASA) Physical Status Classification of I or II. Participants must be able to read and understand English or Spanish, provide assent with parental or guardian consent, and have access to a smartphone compatible with the home sleep monitoring application.

Participants will be excluded if they have a prior diagnosis of SDB or OSA, history of adenotonsillectomy, craniofacial syndromes or conditions known to substantially alter craniofacial morphology, prior or current orthodontic treatment, or prior orthognathic surgery. These exclusion criteria were selected to reduce heterogeneity in upper airway anatomy and SDB risk factors that could confound interpretation of physiologic sleep and craniofacial outcomes.

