Psychosocial Outcomes. Children classified as high-risk for SDB are expected to demonstrate greater symptoms of anxiety, depression, perceived stress, and daytime sleepiness compared with children classified as low-risk. SDB symptoms have been positively associated with depression, anxiety, attention problems, and reduced adaptability in school-aged children, and a recent meta-analysis estimated an overall 28% prevalence of depression among children with or at high risk for OSA, approximately two-fold higher than among children without OSA [56,57,58]. School-aged children with OSA have also demonstrated significantly higher scores on the Spence Children’s Anxiety Scale and Children’s Depression Inventory compared with controls, with symptom severity correlating with disease duration and hypoxia burden [59]. The inclusion of validated psychosocial instruments in this protocol allows for characterization of these associations within a dental setting where such measures are not routinely collected.

Exploratory Craniofacial Outcomes. Among participants with clinically available lateral cephalometric radiographs, exploratory analyses may identify craniofacial characteristics associated with increased SDB risk. A systematic review and meta-analysis found that children with OSA tend to present with mandibular retrognathia (reduced SNB), increased sagittal skeletal jaw discrepancy (increased ANB), and a steeper mandibular plane angle (increased FH-MP) compared with controls [5]. Additional features described in the literature include increased lower anterior facial height, narrower maxillary arch width, and reduced anteroposterior dimensions of the bony nasopharynx [11,60]. Because radiographs are available only for a subset of participants and are obtained through routine clinical care rather than a standardized research imaging protocol, this subset likely represents an orthodontically indicated subpopulation enriched for skeletal and dental anomalies rather than a random sample of the broader pediatric dental clinic population. Accordingly, cephalometric findings may not be generalizable to all children seen in pediatric dental settings, and between-group differences should be interpreted with this selection bias in mind. These analyses are intended to generate preliminary data and inform future hypothesis-driven investigations.

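### Cephalograms taken up to six months after baseline are accepted without a pre-treatment condition, so the enrolment exclusion of orthodontic treatment does not fully protect the exploratory craniofacial measurements

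*Protocol article*

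**What the plan says.** Four parts of the protocol article bear on this.

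- **Eligibility (section 2.3).** Children are excluded for "prior or current orthodontic treatment, or prior orthognathic surgery". The reason given for the exclusions is heterogeneity that "could confound interpretation of physiologic sleep and craniofacial outcomes". Section 3.2 places confirmation of eligibility at the start of the baseline visit. Nothing in the article deals with treatment begun after that.
- **Film source and window (section 2.7).** The analysis uses "clinically available lateral cephalometric radiographs obtained as part of routine dental or orthodontic care". On timing: "Clinically obtained lateral cephalometric radiograph within six months prior to or within six months after the baseline study visit or enrollment will be used". The Table 1 footnote repeats this window, again with no condition on treatment.
- **Choice among films (section 2.7).** With more than one film, "the image obtained closest to the baseline study visit will be selected for analysis".
- **Who will have films (section 4).** The article expects that "this subset likely represents an orthodontically indicated subpopulation enriched for skeletal and dental anomalies". It draws the consequence for selection bias, but does not mention treatment begun before the film was taken.

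The outcomes in section 2.8.3 include dental anterior–posterior, dental vertical and soft tissue profile values as well as skeletal ones. Section 2.9 compares them between risk groups with a t-test or Mann–Whitney test and reports effect sizes with 95% confidence intervals for planning later studies.

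**The concern.** The plan itself names orthodontic treatment as a source of heterogeneity in the craniofacial outcomes. The exclusion settles which children enter the study. It does not settle the state of the teeth and jaws on the day the film is taken, which may be up to six months later. The children with films are expected to be those with an orthodontic reason for having one, and they are also the children most likely to start treatment. Dental position and soft tissue profile are what such treatment sets out to change.

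At stake is the quality of the preliminary effect sizes. Treated films would add variation unrelated to sleep-disordered breathing. If treatment started more often in one risk group, they would also shift the contrast. The planned comparison is unadjusted, so no stated later step would remove either effect.

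**Working it through.** The plan gives no figure to reproduce. The check is one of dates, followed by a simple bound.

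**1. Which part of the window is protected.** The window is 6 months before plus 6 months after baseline, 12 months in all. If the exclusion is applied correctly, a film from the first 6 months is untreated. The second 6 months, half of the window, has no such protection.

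**2. What the closest-to-baseline rule does.** The dates below are illustrative.

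| Films available | Film chosen | Treated? |
|---|---|---|
| Untreated at +1 month, treated at +3 | +1 (1 < 3) | No |
| Untreated at −2 months, treated at +3 | −2 (2 < 3) | No |
| Untreated at −4 months, treated at +3 | +3 (3 < 4) | Yes |
| Treated at +3 months only | +3 | Yes |

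An untreated film after baseline always precedes a treated one and so is always nearer to baseline. The rule therefore protects any child who has such a film. It fails in the last two rows. In the third row it passes over an untreated film that was available.

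**3. Effect on the group contrast.** Let p_H and p_L be the shares of treated films in the high-risk and low-risk groups, and δ a common shift due to treatment in SD units. Then

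bias in the mean difference = δ × (p_H − p_L).

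The documents give none of these quantities, so all values are assumptions.

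| Difference in share | δ = 0.5 SD | δ = 1 SD |
|---|---|---|
| 0 (equal shares) | 0 | 0 |
| 0.1 | 0.05 SD | 0.1 SD |
| 0.2 | 0.10 SD | 0.2 SD |
| 0.3 | 0.15 SD | 0.3 SD |

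If treatment moves different children in different directions, the mean shift is smaller than δ and the bias is smaller too. For scale, section 2.9 treats a Cohen's d of about 0.20 as small.

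**4. Effect on the spread.** With share p treated in both groups and the same common shift, the within-group variance rises by p(1 − p)δ². At δ = 1 SD:

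- p = 0.1: 0.1 × 0.9 = 0.09, so the SD is multiplied by √1.09 = 1.04.
- p = 0.2: 0.2 × 0.8 = 0.16, so √1.16 = 1.08.
- p = 0.3: 0.3 × 0.7 = 0.21, so √1.21 = 1.10.

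Equal shares therefore leave the mean difference unbiased but shrink a standardised effect slightly, by a factor of 1/1.10 = 0.91 in the last case.

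**The case against.** The two sections do not contradict each other: one decides who enrols and the other which film is read. What is missing is a qualifier, and a journal article may leave film-level detail to the full protocol. That carries some weight, but section 2.7 does fix the source, the window and the selection rule, and the rule as written can prefer a treated film to an untreated one.

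A reader might infer that treated films will in fact be used, or used often. The documents do not support this. A child with an orthodontic indication is not necessarily a treated child, and a film taken after enrolment may well be the planning record. The problem needs a child who starts treatment and is imaged under it within six months, and who has neither an untreated post-baseline film nor a pre-baseline film at least as near. This objection stands, and it narrows the point considerably.

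A reader might also take 0.1 to 0.3 SD as the expected bias. It is a one-sided case built on an unsourced shift, and it vanishes when the shares are equal. Section 3.4 has parents of high-risk children told the screening result and advised to seek follow-up, and Table 1 places this notice at baseline. That is a conceivable route to unequal care, but nothing shows that it changes orthodontic starts.

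Finally, the sleep-related differences that section 4 emphasises are mainly skeletal, and no material effect on those has been shown here. The analysis is labelled exploratory, and selection bias is acknowledged. These caveats limit inference but do not cover treatment before the film.

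**Conclusion.** The point holds as a possibility left open by the stated rules. A film taken after treatment starts can be used when it is the child's only film or lies nearer to baseline than an untreated pre-baseline film. The frequency cannot be calculated, because the article does not say how many children will have films, how many of those films will follow baseline, or how many children will start treatment.

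The consequence is confined to the exploratory cephalometric comparison, chiefly the dental and soft tissue values; the primary analysis and the sample size are untouched. Added variance is the likelier cost. Bias requires unequal treated shares or unequal shifts: under a common shift of 1 SD it is at most 0.1 to 0.3 SD for differences in share of 0.1 to 0.3, and zero for equal shares. This is a minor improvement to the plan. It is not evidence that the craniofacial results will be biased.

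**What to change.** In section 2.7, and in the Table 1 footnote to match, state that only radiographs taken before the start of any orthodontic or orthopaedic appliance are eligible, and that the one closest to baseline among these is used. Take treatment status at the film date from the clinical record or, where it is not recorded, judge it from appliances visible on the film.

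The cost is one sentence and one extra item to extract per film. No additional radiograph or visit is needed, and pre-treatment films after baseline stay eligible. There are two drawbacks: a few films may be lost from an already small exploratory subset, and treatment started elsewhere may not appear in the record, so the check on the film itself is needed as a fallback.

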### 2.8. Outcome Measures

#### 2.8.1. Primary Outcome

The primary outcome will be physiologic sleep parameters obtained from the wearable home sleep monitoring device, including the sAHI, sRDI, SAI, and SQI. The sAHI is an automated, FDA-cleared measure of apnea and hypopnea events per hour that quantifies respiratory disturbance burden during sleep, which will be reported at both ≥3% and ≥4% oxygen desaturation thresholds with additional obstructive and central subtype differentiation. The total AHI at 3% desaturation (AHI3%) is consistent with the American Academy of Sleep Medicine (AASM) recommended scoring rule [44] and the total AHI at 4% desaturation (AHI4%) corresponds to the Centers for Medicare & Medicaid Services (CMS) reimbursement criterion [45]. The sRDI captures apnea and hypopnea events as well as arousal-related respiratory disturbances that may not be associated with oxygen desaturation but nonetheless contribute to sleep fragmentation. This broader scope may provide a more comprehensive assessment of respiratory disturbance burden than indices based solely on desaturation-linked events [46,47,48]. Because the wearable device estimates respiratory event indices using CPC analysis rather than direct airflow measurement, device-derived values are not equivalent to PSG-scored AHI; this distinction will be acknowledged in the interpretation of the results. This study is designed as a screening concordance and feasibility investigation, not a diagnostic accuracy study; accordingly, PSG is not included as a reference standard, and findings should be interpreted as characterizing associations between screening-level risk classification and physiologic sleep parameters rather than as establishing diagnostic performance.

In addition to respiratory event indices, two composite cardiopulmonary coupling-derived metrics will be examined. The SAI is a CPC-derived metric that detects cyclic heart rate variations (bradycardia during apneic events followed by relative tachycardia upon breathing resumption) reflecting the autonomic cardiac response to intermittent hypoxemia during unstable breathing. This cardiac-based approach may be particularly relevant in pediatric populations, where apneic events are often shorter and may not meet conventional oximetry desaturation thresholds [49,50]. The SQI is a composite metric derived from CPC analysis that integrates biomarkers of sleep stability, duration, and fragmentation to characterize overall sleep health. Age- and sex-specific normative values have been established for the pediatric age range relevant to this study [34,51].

For participants with two or three qualifying nights, physiological sleep outcomes (CPC, sAHI, sRDI, SAI, and SQI) will be averaged across qualifying nights to generate participant-level outcome measures and compared between PSQ-based SDB risk groups.

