where $Z_{1-\alpha /2}$ = 1.96 (corresponding to a two-sided significance level of α = 0.05), $Z_{1-\beta }$ = 0.8416 (corresponding to 80% statistical power), and d = 0.80 (Cohen’s d, representing a large standardized effect size). Substituting these values yields$$n=2{\left(\frac{1.96+0.8416}{0.80}\right)}^{2}=2{\left(\frac{2.8016}{0.80}\right)}^{2}=2{\left(3.502\right)}^{2}=2\left(12.264\right)\approx 25\;\mathrm{per}\;\mathrm{group}$$

This yields a minimum of 25 participants per group. Enrollment was set at 30 per group (*N* = 60 total) to accommodate an anticipated attrition rate of approximately 20%, accounting for incomplete recordings, data quality exclusions, and participant withdrawal while preserving adequate statistical power for the primary analysis.

This study is powered to address the primary aim only. Secondary and exploratory analyses are intended to generate preliminary effect size estimates and variability data to inform future hypothesis-driven studies. Up to 300 individuals may be screened to achieve target enrollment, reflecting the expected distribution of risk classification within the clinic population and anticipated exclusions. A stratified quota sampling approach will be used to ensure balanced representation of each PSQ-defined risk group, a design feature that does not alter the cross-sectional nature of the study but ensures adequate statistical power for between-group comparisons. Participants who discontinue or have incomplete data will not be replaced.

The study was approved by the Institutional Review Board of the University of North Carolina (UNC) at Chapel Hill (IRB#25-3218, 26 January 2026) and registered at ClinicalTrials.gov (NCT07581938, 5 May 2026). Recruitment and follow-up procedures will be conducted between May 2026 and June 2027. This protocol is reported in accordance with the Standard Protocol Items: Recommendations for Interventional Trials (SPIRIT) 2025 statement [36] and adapted accordingly for this prospective, cross-sectional observational study. A completed SPIRIT 2025 checklist is provided as Supplementary Table S1.

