### 2.5. Home Sleep Monitoring Methods

Objective physiologic sleep data will be collected using the SleepImage Ring, an FDA-cleared wearable home sleep monitoring device, and analyzed using the FDA-cleared SleepImage System (Version 2.28, MyCardio LLC, Denver, CO, USA). Following completion of baseline assessments, participants will receive the device along with standardized instructions for use, charging, and smartphone application synchronization. Participants and their parents or guardians will be instructed to maintain usual sleep routines throughout the monitoring period.

Participants will wear the device during sleep for a minimum of three consecutive nights. To accommodate scheduling challenges, missed nights, and device return logistics, participants will be permitted up to three weeks to complete the required monitoring period. Physiologic sleep data will be collected passively during sleep and transmitted through a secure, HIPAA-compliant platform.

Primary physiologic sleep outcomes will include the cardiopulmonary coupling (CPC) software-derived Apnea-Hypopnea Index (sAHI), software-derived Respiratory Disturbance Index (sRDI), Sleep Apnea Indicator (SAI), and Sleep Quality Index (SQI), provided as continuous data. To ensure adequate data quality, only recordings with an average signal quality of at least 50% and a minimum sleep duration of four hours per night will be included in analyses. A minimum of two qualifying recording nights will be required for a participant’s data to be included in the primary analysis. Participants with only one qualifying night will be excluded from the primary analysis but will be retained for sensitivity analyses.

Adherence will be supported through brief telephone check-ins approximately one and two weeks following device distribution to address technical questions and encourage compliance. Home-based monitoring was selected over laboratory polysomnography to enable assessment within the participant’s natural sleep environment while minimizing burden and supporting feasibility within a pediatric dental setting.

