Exploratory craniofacial analyses will be conducted among the subset of participants with available lateral cephalometric radiographs. Cephalometric measurements will be summarized descriptively and compared between risk groups using independent-samples *t*-tests or Mann–Whitney U tests. Given the anticipated smaller sample size and exploratory nature of these analyses, findings will be reported as effect size estimates with 95% confidence intervals to inform future study design.

No formal adjustment for multiple comparisons will be applied to secondary and exploratory analyses, as these are intended to generate preliminary estimates rather than confirmatory conclusions. All statistical analyses will be performed using SPSS (v. 31, IBM SPSS Statistics, IBM Corp., Armonk, NY, USA). Statistical significance will be evaluated using two-sided tests with an α level of 0.05.

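### Four device measures share primary status with no stated success rule, while the sample size covers one comparison at 0.05

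*Protocol article*

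**What the plan says.** Section 2.8.1 defines the primary outcome as a set: "The primary outcome will be physiologic sleep parameters obtained from the wearable home sleep monitoring device, including the sAHI, sRDI, SAI, and SQI". Section 2.5 does the same in the plural, starting "Primary physiologic sleep outcomes will include the cardiopulmonary coupling (CPC) software-derived Apnea-Hypopnea Index (sAHI), software-derived Respiratory Disturbance Index (sRDI), Sleep Apnea Indicator (SAI), and Sleep", and Section 2.9 names the same four in its primary analysis. Each is averaged over qualifying nights and compared between PSQ groups by t-test or Mann–Whitney U test. None is ranked above the others.

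Two details widen the set or leave it open. Section 2.8.1 says of sAHI that it will be "reported at both ≥3% and ≥4% oxygen desaturation thresholds with additional obstructive and central subtype differentiation", without saying which version the primary test uses. The last paragraph of the same section gives a longer list for averaging and group comparison: "physiological sleep outcomes (CPC, sAHI, sRDI, SAI, and SQI) will be averaged across qualifying nights". CPC is not among the four measures named in Section 2.9.

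On error control, Section 2.9 says: "Statistical significance will be evaluated using two-sided tests with an α level of 0.05". It also says: "No formal adjustment for multiple comparisons will be applied to secondary and exploratory analyses". The reason it gives is that those analyses are not confirmatory. It is silent on the primary family.

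Section 2.1 derives the sample size from the formula for two independent means, with alpha 0.05 two-sided, 80% power and d = 0.80, giving 25 per group. It then states: "This study is powered to address the primary aim only". The effect size is not tied to any one of the four measures.

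**The concern.** A sample size and a significance level only have meaning against a rule for success. Here there are four equal candidates and no rule. A reader of the results could not tell whether the primary aim is met by one significant measure, by all four, or by one in particular.

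Two things are at stake. If any one of four results below 0.05 can be presented as a positive primary finding, the false-positive chance is above the 5% that the alpha level implies. And the claim of 80% power belongs to neither of the natural success rules. The undefined sAHI version adds a further choice, which could be made after the data are seen.

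**Working it through.** **Inputs from the protocol article.** Four measures in the primary analysis (Sections 2.5, 2.8.1, 2.9); alpha 0.05 two-sided (Sections 2.1, 2.9); power 80%, d = 0.80, 25 per group (Section 2.1).

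**Assumption.** The documents give no correlation between the measures. A common correlation ρ from 0 to 0.9 is used, with SQI reversed so that higher is worse for all four.

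**1. The protocol's own figure.** n = 2 × ((1.96 + 0.8416)/0.80)² = 24.53, rounded up to 25 per group. The figure reproduces. It describes exactly one comparison at an unsplit 0.05. By the same normal approximation, power at 25 per group is 80.7%.

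**2. False-positive chance if any one of four counts.** With independent measures: 1 − 0.95⁴ = 0.185. With correlated measures, by simulating four equicorrelated normal statistics, each tested against ±1.96 with no true difference:

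| ρ | At least one false positive |
|---|---|
| 0 | 18.5% |
| 0.5 | about 16% |
| 0.8 | about 11% |
| 0.9 | about 9% |

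Every value exceeds 5%.

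**3. Power under the two natural success rules.** Suppose d = 0.80 holds for all four measures at 25 per group. Each test statistic then has mean 0.80 × √(25/2) = 2.83. Simulating the four with no adjustment gives:

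| ρ | Any one significant | All four significant |
|---|---|---|
| 0.5 | about 97% | about 57% |
| 0.8 | about 92% | about 67% |

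The stated 80% is the power for one measure taken alone. It lies between the two rules and matches neither.

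**4. Power if the four stay primary and are tested by Holm at family-wise 0.05.** Under the same assumptions:

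| ρ | Average power per measure | At least one rejection |
|---|---|---|
| 0.5 | about 72% | about 89% |
| 0.8 | about 71% | about 80% |

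**5. Power if one measure is the sole primary.** Step 1 applies unchanged: 25 evaluable per group, about 80% power, no alpha split.

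**The case against.** The strongest defence is the design. Sections 2.1, 2.8.1 and 4 describe a screening concordance and feasibility study that characterises associations. No treatment decision hangs on one p-value. Section 4 states an expected direction for every measure, and Section 2.9 commits to reporting effect sizes. If all four results are shown openly, selective claims are harder to make. This stands, and it lowers the severity. It does not remove the problem, because Section 2.1 claims power for the primary aim and Section 2.9 reserves the estimation-only excuse for secondary and exploratory analyses.

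A second defence is that multiplicity procedures are commonly left to a statistical analysis plan, which is not shown. Silence here does not prove that no adjustment will be made, and the point is worded accordingly. But the article itself fixes four primaries against a sample size for one comparison, and a rule added later would not by itself reconcile the two.

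A third is that the measures come from one device and must overlap. Section 2.8.1 describes sRDI as including the apnea and hypopnea events. Strong correlation is therefore plausible, and the 18.5% for independence is an upper end, not a best guess. SQI may correlate less, so the range is the fair statement.

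A reader might go further and count nine primary tests: two thresholds by total, obstructive and central sAHI, plus the other three, giving 37% under independence. The text does not support that. The sAHI versions are to be reported, and nothing says that each is tested; the primary analysis in Section 2.9 lists four parameters. What stands is narrower: the version entering that test is not identified.

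**Conclusion.** The point holds for four measures. They are co-equal primaries, each tested at 0.05, with no success rule or multiplicity rule stated for them in the article, and the sample size is that of a single comparison. The false-positive chance for any one significant result is about 9% to 18.5% over assumed correlations of 0.9 down to 0. The stated 80% power fits neither the any-one nor the all-four rule, given d = 0.80 on every measure, 25 per group and the normal approximation.

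Two further inferences should be resisted. A plain Bonferroni split (0.0125 each) would put power for a given measure at 63% with 25 per group on the protocol's own method, but Holm loses less and is the fairer comparison. Nor do the documents show that total AHI at 3% desaturation is the right primary. Section 2.8.1 links it to a recommended scoring rule, yet also argues that sRDI may be more comprehensive, and that SAI may suit children whose events do not reach desaturation thresholds.

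Severity: should be fixed, not fatal, given the feasibility and association framing.

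**What to change.** Before analysis, and before any group comparison is looked at, name one device measure as the sole primary for the 0.05 test. If it is sAHI, state the desaturation threshold and whether it is total, obstructive or central. Make the other measures and sAHI versions secondary, reported with 95% confidence intervals. Say whether CPC in the last paragraph of Section 2.8.1 is an outcome, and if so at what level. Total AHI at 3% desaturation is one candidate; the choice is the investigators'. This keeps the calculation of 25 per group valid and needs no extra participants.

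If all four are to stay primary, fix one sAHI version, test the four by Holm at family-wise 0.05, state what counts as success, and restate the power. On the assumptions above (d = 0.80 for all four, 25 per group, correlation 0.5 to 0.8), that is about 71% to 72% on average per measure and 80% to 89% for at least one rejection.

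The cost is a wording amendment to Sections 2.1, 2.5, 2.8.1 and 2.9, submitted to the IRB as Section 3.4 requires. The price is that either three measures lose confirmatory status or the stated power per measure becomes lower.
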